## Abstract

**Background:**

Globally, women with disabilities are less likely to have access to family planning services compared to their peers without disabilities. However, evidence of effective interventions for promoting their sexual and reproductive health and rights remains limited, particularly in low- and middle-income settings. To help address disparities, an inclusive sexual and reproductive health project was developed to increase access to modern contraceptive methods and reduce unmet need for family planning for women of reproductive age with disabilities in Kaduna city, Nigeria. The project uses demand-side, supply-side and contextual interventions, with an adaptive management approach. This protocol presents a study to evaluate the project’s impact.

**Methods:**

A pragmatic cluster-randomized controlled trial design with surveys at baseline and endline will be used to evaluate interventions delivered for at least 1 year at health facility and community levels in comparison to ‘standard’ state provision of family planning services, in the context of state-wide and national broadcast media and advocacy. Randomization will be conducted based on the health facility catchment area, with 19 clusters in the intervention arm and 18 in the control arm. The primary outcome measure will be access to family planning. It was calculated that at least 950 women aged 18 to 49 years with disabilities (475 in each arm) will be recruited to detect a 50% increase in access compared to the control arm. For each woman with disabilities enrolled, a neighbouring woman without disabilities in the same cluster and age group will be recruited to assess whether the intervention has a specific effect amongst women with disabilities. The trial will be complemented by an integrated process evaluation. Ethical approval for the study has been given by the National Health Research Ethics Committee of Nigeria and London School of Hygiene & Tropical Medicine.

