### Sample size {14}

Calculations were conducted in Microsoft Excel [31], based on Hayes & Bennett [32]. The assumptions, as summarized in Table 4, were used in determining the likely number of women 18–49 years with disabilities who will be living in the catchment areas of the healthcare facilities, as this is the target population for the evaluation. Various plausible estimates of the between-cluster coefficient of variation (*k*) and effect sizes were explored. Determination of the sample size was guided by the number of areas that the Sightsavers team has capacity and funding to reach, and security concerns limiting implementation to Kaduna city. Assuming *k* = 0.3, a 5% significance level, and 80% power, the trial will be able to detect a risk ratio of 1.5 (i.e. a 50% increase in access compared to the control arm) with 25 women with disabilities interviewed in each cluster. This design will require approximately 20,000 households to be screened for eligible women. It was originally intended to have 19 clusters per arm (a total of 38 clusters overall); however, it was only possible to identify a total of 37 clusters in Kaduna city, consequently 19 clusters were assigned to the intervention arm and 18 clusters to the control arm.

**Table 4 Tab4:** Assumed and derived values for the IFPLAN cluster randomized controlled trial sample size calculations

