**Assumptions:**	
Proportion of women aged 18–49 years	20.0%
Proportion of women 18–49 years who are disabled based on Washington Group Questions^a^	0.7%
Proportion of women 18–49 years with depression or anxiety^b^	6.0%
Estimated overlap between the above	30%
Number of people in each cluster	10,000
Proportion of women who have ‘access’ to family planning	25%

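### The abstract's recruitment target of 950 women (475 per arm) belongs to the 38-cluster design; the 19/18 split at 25 women per cluster gives 925 (475 and 450).

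*Protocol article*

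**What the plan says.** The abstract (Methods) gives 19 clusters in the intervention arm and 18 in the control arm. It then states that "at least 950 women aged 18 to 49 years with disabilities (475 in each arm) will be recruited" in order to detect a 50% increase in access, and that each woman with disabilities will be paired with a neighbour without disabilities.

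The section Sample size {14} cites the Hayes and Bennett method and assumes a between-cluster coefficient of variation of 0.3. With "a 5% significance level, and 80% power, the trial will be able to detect a risk ratio of 1.5", it plans the trial "with 25 women with disabilities interviewed in each cluster". It goes on: "It was originally intended to have 19 clusters per arm (a total of 38 clusters overall"). Only 37 clusters could be found, so "19 clusters were assigned to the intervention arm and 18 clusters to the control arm". Table 4 puts control-arm access at 25%.

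The sections on eligibility, sequence generation and blinding agree on 37 clusters or on the 19/18 split. The article gives neither 925 nor 450, and mentions no larger number of women in control clusters.

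**The concern.** The abstract updates the cluster count to 19 and 18 but keeps a participant total and an equal-arm statement that need 19 clusters on each side. Both figures are current text, so this is not a difference between versions.

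A planned sample size is what the final report is compared with. If the trial enrolled exactly 25 women in each of its 37 clusters, it would appear to miss its published minimum by 25, with the whole deficit in the control arm, although it had delivered its own design. The sample-size section also states power before it mentions the lost cluster and gives no separate figure for 19 and 18, so a reader cannot tell whether the loss matters.

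**Working it through.** **Inputs**

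- Control proportion p0 = 0.25 (Table 4).
- Risk ratio 1.5, so p1 = 1.5 × 0.25 = 0.375 (Sample size {14}).
- k = 0.3, m = 25 women per cluster, 5% significance, 80% power (Sample size {14}).
- Sidedness is not stated. I assume two-sided, so (1.960 + 0.842)² = 7.849.

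**Step 1. Reproduce the plan's figure.** The Hayes and Bennett formula for proportions is

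c = 1 + 7.849 × [p0(1−p0)/m + p1(1−p1)/m + k²(p0² + p1²)] / (p1 − p0)²

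- Binomial terms: 0.1875/25 + 0.2344/25 = 0.01688.
- Between-cluster term: 0.09 × (0.0625 + 0.1406) = 0.01828.
- Sum 0.03516; divided by 0.125² = 0.015625 this is 2.25.
- c = 1 + 7.849 × 2.25 = 18.66, rounded up to 19 per arm.
- 19 × 25 = 475 per arm; 2 × 475 = 950.

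The stated 950 is therefore the output for 19 + 19 clusters. Other readings do not give it: without the added cluster, c = 17.66, hence 18 per arm and 900 women; one-sided with the added cluster, c = 14.91, hence 15 per arm and 750.

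**Step 2. Count for the design being run**

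| | Clusters | Women at 25 per cluster | Abstract |
|---|---|---|---|
| Intervention | 19 | 475 | 475 |
| Control | 18 | 450 | 475 |
| Total | 37 | 925 | at least 950 |

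The shortfall is 25 women: 25/950 = 2.6% of the total and 25/475 = 5.3% of the control-arm figure. One neighbour is recruited per woman, so the matched group is also 925.

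**Step 3. Number per cluster that would deliver the stated figures**

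- 475 in 18 control clusters: 475/18 = 26.4 per cluster.
- 950 spread over 37 clusters: 950/37 = 25.7 per cluster.

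**Step 4. Power for a risk ratio of 1.5.** The variance contributed by one cluster is

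- intervention: 0.2344/25 + 0.09 × 0.1406 = 0.02203;
- control: 0.1875/25 + 0.09 × 0.0625 = 0.01313.

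Power = Φ(0.125/√V − 1.960). V is the sum of each arm's variance divided by its cluster count, less one cluster per arm to match the added cluster in the formula.

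- 19 + 19: V = 0.02203/18 + 0.01313/18 = 0.001953; 0.125/√V = 2.828; power 80.7%.
- 19 + 18: V = 0.02203/18 + 0.01313/17 = 0.001996; 0.125/√V = 2.798; power 79.9%.

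Without the one-cluster correction the two figures are 82.8% and 82.0%. A noncentral t calculation on the full cluster counts also gives 80.7% and 79.9%. With the correction, the risk ratio detectable at 80% power is about 1.49 for 19 + 19 and about 1.50 for 19 + 18. With 950 women in 37 clusters, either 475 per arm or spread evenly, power is 80.4%.

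**The case against.** The best defence is that the target is worded as a minimum and that nothing calls 25 per cluster a cap. Table 4 derives about 130 eligible women per cluster, so one or two more in each control cluster looks feasible. The loss of a cluster is also openly explained in the sample-size section, and the abstract presents the 950 as the result of a calculation.

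Much of this stands. A reader might infer that the trial cannot reach 950. The documents do not support that: on the plan's own assumptions 26.4 women per control cluster is within reach. A reader might also infer that the power claim fails because it rests on a design that is not being run. That does not follow either, since 79.9% rounds to the stated 80% and the detectable risk ratio is still about 1.50. Nor do the documents show whether power was recalculated after the cluster was lost; they are silent on it.

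The contradiction itself remains. The disclosure covers the cluster count but not the number of women, and no larger number per control cluster is planned anywhere. If a larger number is intended, that too has to be written down.

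**Conclusion.** The concern holds as an inconsistent recruitment figure. The abstract's 950, with 475 in each arm, is the total for 19 + 19 clusters. The stated 19/18 split at 25 per cluster gives 925, with 475 intervention and 450 control. The counts need no assumption beyond the article's own cluster numbers and 25 women per cluster.

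The effect on power is under one percentage point. That result rests on the article's 25% control access and k = 0.3, on a two-sided 5% test (my assumption, the reading that reproduces 950) and on the one-cluster-per-arm correction. The stated 80% is essentially unaffected. Randomization and the planned analysis are not affected.

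**What to change.** Reconcile the abstract with Sample size {14} in one of two ways. The documents do not show which is intended.

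1. Restate the target as 925 women with disabilities (475 intervention, 450 control) and 925 matched neighbours.
2. Keep 950 and state the number per cluster that delivers it: an average of about 26.4 in each control cluster with 25 in each intervention cluster, or about 25.7 across all 37.

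In either case, add to Sample size {14} that with 19 and 18 clusters of 25, power for a risk ratio of 1.5 is about 79.9% (k = 0.3, two-sided 5%, one-cluster-per-arm correction), against 80.7% for 19 + 19. Under the second option it is 80.4%.

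The first option costs a text correction only. The second adds 25 women with disabilities and 25 neighbours beyond what 25 per cluster yields, with the household screening needed to find them.

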**Discussion:**

Defining access to services is complex, as it is not a single variable that can be measured directly and need for family planning is subjectively defined. Consequently, we have conceptualized ‘access to family planning’ based on a composite of beliefs about using services if needed.

**Trial registration:**

ISRCTN registry ISRCTN12671153. Retrospectively registered on 17/04/2023.

**Supplementary Information:**

The online version contains supplementary material available at 10.1186/s13063-023-07892-y.

## Administrative information

Note: the numbers in curly brackets in this protocol refer to SPIRIT checklist item numbers. The order of the items has been modified to group similar items (see http://www.equator-network.org/reporting-guidelines/spirit-2013-statement-defining-standard-protocol-items-for-clinical-trials/).

## Introduction

### Background and rationale {6a}

Target 3.7 of the Sustainable Development Goals (SDGs) calls on countries to ‘ensure *universal* access to sexual and reproductive healthcare services, including for family planning, information and education, and the integration of reproductive health into national strategies and programmes’ by 2030 [1]. Access to these services is variable within, as well as between countries, and certain groups are particularly left behind, such as women with disabilities. The United Nations Convention on the Rights of Persons with Disabilities describes people with disabilities as ‘including those who have long term physical, mental, intellectual or sensory impairments which in interaction with various barriers may hinder their full and effective participation in society on an equal basis with others’. Globally, women with disabilities make up approximately 15% of the population and they are less likely to have access to family planning services than other women of the same age [2]. This inequity occurs because women with disabilities experience multiple barriers to accessing family planning services. These barriers broadly include the following: lack of education on sexual and reproductive health; negative family, community and provider attitudes; lack of alternative communication formats; lack of accessible transport and infrastructure; and financial constraints [3, 4]. Consequently, this SDG target will not be achieved unless family planning services are accessible to women with disabilities [5]. Despite this inequity, research on the sexual health of people with disabilities and evidence of effective interventions for promoting their sexual and reproductive health and rights (SRHR) remains limited, particularly in low- and middle-income country (LMICs) settings [6, 7].

Nigeria has 54 million women of reproductive age (15–49 years) [8]. Amongst women in this age group, 0.6% were reported in the 2018 Demographic Health Survey (DHS) to have a disability ([name], unpublished observations). Moreover, this estimated prevalence does not include any type of psychosocial disability, such as depression or anxiety. Evidence from Lagos State, Nigeria, showed that amongst survey respondents aged 18–75 years old the weighted prevalence of depression and generalized anxiety was 5.5% and 3.5% respectively, with 1.2% experiencing both [9]. The prevalence of disability amongst women of reproductive age in Nigeria is therefore likely to be much higher than 0.6% when psychosocial disabilities are included.

Access to family planning in Nigeria varies by state, with the lowest service coverage in the northern states [10]. DHS data from Kaduna, a northern state with over 9 million people, has shown that just 13.7% of women report currently using a modern method of family planning [10], despite modern contraceptives being generally seen as acceptable across Nigeria [11]. Low uptake in Kaduna has been reportedly due to lack of empowerment amongst women to make decisions on contraception; requirement for husband’s permission to access services; provider insistence on spousal consent; promotion of traditional methods by religious leaders; and high out of pocket expenses—both real and perceived [12]. Utilization of family planning services in Nigeria has also more recently been disrupted by the COVID-19 pandemic, affecting both the demand and supply side [13, 14].

Further analysis of the 2018 DHS data shows that the met need for family planning was almost 10 percentage points higher amongst women without disabilities (28%) than for women with disabilities (19%) ([name], unpublished observations). Identified barriers to accessing reproductive health services amongst women with disabilities in Nigeria, include significantly lower awareness of family planning [15], as well as impairment-specific barriers. For instance, women with hearing impairment reported embarrassment about asking questions in the presence of an interpreter, and communication difficulties and cost as key barriers to access [16, 17]. Improving access to healthcare requires a holistic approach to address the many dimensions of access [18]. Therefore, correcting this inequality in access and reaching the SDG target in Kaduna will require a comprehensive intervention that is inclusive of women with disabilities.

To help address these disparities, an inclusive sexual and reproductive health project will be designed and delivered by a consortium led by the international non-governmental organization (iNGO) Sightsavers, supported by BBC Media Action under the Disability Inclusive Development (DID) programme, and in partnership with the Joint National Association of Persons with Disability (JONAPWD) and the Network of Disabled Women (NDW) in Nigeria. The Inclusive Family Planning (IFPLAN) project aims to increase access to modern contraceptive methods and reduce unmet need for family planning for women with disabilities aged 15–49 years in Kaduna city, Nigeria. The project’s objectives include increasing knowledge of, intention to use, and perceived support amongst women with disabilities in accessing available family planning services; delivery of inclusive, accessible healthcare services and information by service providers; and meaningful engagement of organizations of persons with disabilities (OPDs) in policy and decision-making processes, and advocacy for disability inclusion in the health sector.

A pragmatic cluster-randomized controlled trial with integrated process evaluation will be undertaken to understand whether the intervention package implemented under the IFPLAN project has increased access to modern contraceptive methods, and reduced unmet need for family planning for women with disabilities. The evaluation, which is being conducted under a separate UK Foreign, Commonwealth, and Development Office (FCDO) programme to the project, is led by London School of Hygiene and Tropical Medicine (LSHTM), in partnership with Oxford Policy Management (OPM) Nigeria under the UK FCDO Programme for Evidence to Inform Disability Action (PENDA).

### Objectives {7}

Informed by the population, intervention, control and outcome (PICO) defined in Table 1, the cluster randomized controlled trial aims to answer the following research questions:Did the intervention increase access to family planning amongst women with disabilities in selected sites in Kaduna city?Did the intervention increase use of family-planning services amongst women with disabilities in selected sites in Kaduna city?Did the intervention reduce the unmet need for family-planning services amongst women with disabilities in selected sites in Kaduna city?

**Table 1 Tab1:** PICO for cluster-randomized controlled trial of the IFPLAN project

Population	Women aged 18^a^–49 years that report at least ‘a lot’ of difficulty on one of the six questions in the Washington Group short set or ‘daily’ and ‘a lot’ to additional questions on depression or anxiety; women in the same neighbourhood and age range without disabilities, in order to determine whether the intervention has a specific effect amongst women with disabilities
Intervention	Components of the IFPLAN project delivered at the health facility and community levels, in the context of state-wide and national broadcast media and advocacy
Control	‘Standard’ provision of family planning services in the state, in the context of state-wide and national broadcast media and advocacy
Outcome	Primary: Access to family planning Secondary: Knowledge, unmet need, and use of family planning

^a^The evaluation will include women aged 18–49 years, as opposed to the target age of 15–49 years in the IFPLAN project, as it was considered not acceptable to interview women under 18 years regarding their sexual and family planning practices, given the sensitive nature of the research topic and the need for caregiver consent for minors to participate

### Trial design {8}

Evaluation of the IFPLAN project will adopt a pragmatic cluster-randomized controlled superiority trial design with two parallel groups [19]. This is a suitable design since the project funds are limited and there is little evidence available about the efficacy of interventions to improve family planning for women with disabilities in such settings. A cluster design was chosen to reduce the likelihood of contamination between the two arms given that interventions are being delivered at health facility and community levels. A more pragmatic rather than explanatory approach was adopted to the trial in order to meet the needs of decision-makers on the utility of IFPLAN in a real-world implementation setting [20].

The unit of randomization will be the health facility catchment area. Within each cluster women aged 18 to 49 years with disabilities will be recruited by the study team. For each woman with disabilities enrolled, a neighbouring woman without disabilities in the same cluster and age group will be recruited. A baseline survey will be conducted prior to implementation of the intervention in December 2022, with an endline survey after completion of at least 1 year of intervention implementation (anticipated for 2024). The trial will be complemented with an integrated process evaluation to describe intervention implementation as delivered, identify mechanisms of impact and explore context dependencies [21].

## Methods: participants, interventions and outcomes

### Study setting {9}

This trial will be conducted in the region in and around Kaduna city, in Kaduna State.

### Eligibility criteria {10}

Cluster eligibility was based on formative work conducted by Sightsavers to identify functioning health facilities offering family planning services in and around Kaduna city—with a total of 74 facilities identified. All types of operational health facilities that offer family planning services to the general public were eligible, including primary, secondary and tertiary facilities, and public and private facilities. Two of the identified facilities were thus excluded as they were military and air force facilities that did not provide services to the general public.

Facility coordinates were subsequently mapped using QGIS and a 0.5-km radius buffer added to each facility to approximate the catchment area [22]. To reduce the likelihood of contamination between clusters, facilities that were within 0.5 km of each other were merged into the same cluster, so that these health facilities were part of the same arm. The expectation being that if assigned to the intervention arm, intervention activities would be implemented in all health facilities and catchment areas in that cluster. This resulted in 13 clusters with 2–4 facilities (total of 34 health facilities).

A Voronoi overlay, whereby polygons are formed around a health facility (or cluster of health facilities) so that the area of the polygon is closest to that health facility (or cluster of health facilities) and no other, was added to the satellite map in QGIS. This was done to get a sense of the geographical areas that might be served by the health facilities in each cluster, and a 0.25 km buffer added between clusters in order to create a combined 0.5 km of separation between clusters. The results of the cluster mapping in QGIS are shown in Fig. 1.

**Fig. 1 Fig1:**
[figure not shown]
Map of IFPLAN research site in Kaduna City, Nigeria. **A** Map to contextualize the location of Kaduna City within Nigeria and the African continent. **B** Health facilities providing family planning services overlaid onto a satellite map of Kaduna city. The cluster boundaries shown are those generated through the use of a Voronoi overlay in QGIS prior to further refinement based on information from health facilities with regard to the communities in their catchment areas

Subsequently, these indicative cluster boundaries were refined by OPM through visits to eligible health facilities. During these site visits, catchment areas were confirmed through discussions with the facility in-charge and verified using the patient register. Communities in catchment areas that either overlapped with health facilities in different clusters or were deemed too insecure by local security experts for the data collection teams to survey were removed. If a health facility’s catchment area completely overlapped with the surrounding facilities, the health facility was removed from the study. The removal of insecure areas will mean that some of the most vulnerable women in Kaduna city will not be included in the trial, which is a limitation of the study. As a result, 13 clusters were excluded from the study, reducing the number of clusters from our desired sample of 38 clusters to 37 eligible clusters in total. A flow diagram to illustrate the selection of health facility catchment areas is outlined in Fig. 2.

